#### Participant timeline {13}

##### Run-in phase (days -7–0)

When patients have signed the informed consent and are included in the study, a smear of their oral mucosa is taken and sent to humatrix AG (Pfungstadt Germany, https://www.stratipharm.de) for pharmacogenotyping and phenotype prediction (day -7, see Fig. 1). During the run-in phase, liver and kidney functions will be assessed, taking the following laboratory values: creatinine, eGFR (calculated using CKD-EPI formula), ASAT, ALAT, gamma GT, and total bilirubin. Additional laboratory values will be determined: TSH, C-reactive protein, serum levels of vitamin B12 (total concentration), vitamin D (25-hydroxy-cholecalciferol), and basic hematology (hemoglobin, total erythrocytes, total thrombocytes, total leukocytes). These values will be reassessed at discharge. Moreover, the patient’s antidepressant medication history including the reasons for discontinuation is documented (see Table 1).

**Fig. 1 Fig1:**
[figure not shown]
Study procedures

**Table 1 Tab1:** Schedule of assessments

Day	Pre-study	Run-in phase		Treatment phase					Follow-up	Clinic discharge
	−8	−7	−7–0	0	7	14	21	28	35, 42..	
Informed consent for trial participation	**x**									
Eligibility (pregnancy test, drug screening, inclusion, & exclusion criteria)	**x**									
Buccal swab (Stratipharm®)		**x**								
Medical history (previous antidepressant therapies)			**x**							
Lab values (basic hematology, creatinine (eGFR), ASAT, ALAT, total bilirubin, gamma-GT, CRP, TSH, vit. B12, and vit. D)			**x**							**x**
Concomitant medication documentation			**x**	**x**	**x**	**x**	**x**	**x**	**x**	**x**
RANDOMIZATION (only if new antidepressant indicated)				**x**						
PGx pharmaceutical recommendation (only arm A)				**x**						
Start NEW antidepressant				**x**						
HAM-D17	**x**			**x**^**a**^	**x**^**c**^	**x**	**x**^**c**^	**x**	**x**	**x**
AE assessment (antidepressant therapy only)					**x**^**c**^	**x**	**x**^**c**^	**x**	**x**	**x**
FIBSER patient self-assessment				**x**^**a**^	**x**^**c**^	**x**	**x**^**c**^	**x**	**x**	**x**
BDI-II patient self-assessment				**x**^**a**^		**x**		**x**	**x**^**b**^	**x**
Blood sample collection (EDTA and serum)						**x**		**x**		

^a^Baseline scoring before the first intake of new antidepressant

^b^BDI-II assessed in two weekly intervals

^c^Only for study arms A and B

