##### Randomization and procedures for arms A and B

If after the run-in phase, at day 0 (±3 days), the treating physician assesses the adjustment to a new antidepressant pharmacotherapy as necessary, and the patient is randomized to either arm A (intervention group) or arm B (control group) (see Fig. 1).

In arm B, the treating physician alone, according to the current standard of care considering clinical factors only, will determine the selection and dosing of the new antidepressant pharmacotherapy. The treating physician and patient will be blinded to the results of the previously conducted pharmacogenotyping for patients randomized to arm B until day 28. For patients in arm B, results from prior pharmacogenetic testing will be interpreted by a clinical pharmacist and made accessible to the treating physician after day 28.

In arm A, a clinical pharmacist will process and evaluate the results from PGx testing (Stratipharm®) in context of the individual patient history as well as current co-medication and forward an individualized recommendation for antidepressant selection and dosing to the treating physician at day 0.

In both arms, the newly prescribed antidepressant pharmacotherapy intake is continuously documented and therapy response observed over a period of 28 days with weekly assessments of adverse events related to the antidepressant medication (using CTCAE version 5.0) and scorings of HAM-D17 (days 0, 7, 14, 21, and 28; ±3 days) as well as patient self-assessments of FIBSER score (days 0, 7, 14, 21, and 28; ±3 days) and BDI-II score (days 0, 14, and 28; ±3 days) (see Table 1).

If patients in either study group remain in the clinic after day 28 (±3 days), a weekly follow-up of HAM-D17, FIBSER, and two-weekly BDI-II are continued until discharge (see Table 1).

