### Assignment of interventions: blinding

#### Who will be blinded {17a}

This is an open-label study, hence no blinding of intervention allocation is possible and needed. However, the genetic data assessed during the run-in phase will only be shared with the treating physician and patients allocated to the control or observational group after day 28 of the treatment phase.

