### Data collection and management

#### Plans for assessment and collection of outcomes {18a}

Outcomes described in section {12} are assessed and collected using validated questionnaires and scoring tools (HAM-D17, FIBSER, BDI-II). FIBSER and BDI-II are patient-self-rated scores where the patients fill the according questionnaires independently [19, 20]. The HAM-D17 score is assessed by a trained rater (e.g., treating physician or specifically designated personnel) [18] who is however, not blinded to the patient allocation. The treating physician does the antidepressant adverse event assessment and grading according to the CTCAE version 5.0 [21]. The described data is collected on paper forms approved by the local ethics committee or directly entered into the patient electronic medical record when appropriate.

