### Statistical methods

#### Statistical methods for primary and secondary outcomes {20a}

The primary outcome of this study is the response rate at day 28 in study arms A and B. The response is defined as a reduction of the HAM-D17 score of at least 50% compared to baseline at day 0. Additionally, the following secondary outcomes are assessed: time to response, remission rate, overall change in HAM-D17 score, laytime in the clinic, change in BDI-II score, change in FIBSER score, and number of AEs related to antidepressant pharmacotherapy. For statistical analyses, the software packages of “IBM SPSS Statistics” and “GraphPad Software” are used. A descriptive statistics analysis for all variables is performed. Fisher’s exact test or *t* test is used to compare pairwise differences between groups and between baseline and follow-up visits as per data type. To measure the correlation between variables, the Spearman coefficient will be used. Significance level is two-sided, *α* = 0.05. For further statistical analyses, adjustments for confounding factors will be taken into account. Any deviation from the original statistical plan will be described and justified in the final trial report.

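### The day-0 HAM-D17 that anchors the primary endpoint must precede first drug intake but not randomisation, and its rater is unblinded, so the baseline may be scored with the arm known

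*Protocol article*

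**What the plan says.** **Endpoint.** Protocol article, {20a}: "The response is defined as a reduction of the HAM-D17 score of at least 50% compared to baseline at day 0". It is judged at day 28.

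**Rater.** Section {18a}: "The HAM-D17 score is assessed by a trained rater (e.g., treating physician or specifically designated personnel"), and the same sentence continues "who is however, not blinded to the patient allocation". Section {17a} says: "This is an open-label study, hence no blinding of intervention allocation is possible and needed".

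**Order of events on day 0.** In Table 1 the day-0 column holds randomisation, the PGx recommendation (arm A only), the start of the new drug and the baseline HAM-D17. Footnote a gives the one timing rule for that score: "Baseline scoring before the first intake of new antidepressant". The section on randomisation and procedures for arms A and B adds:
- The decision that triggers randomisation: "If after the run-in phase, at day 0 (±3 days), the treating physician assesses the adjustment to a new antidepressant pharmacotherapy as necessary".
- The pharmacist's task in arm A: "forward an individualized recommendation for antidepressant selection and dosing to the treating physician at day 0".
- The rating windows: "scorings of HAM-D17 (days 0, 7, 14, 21, and 28; ±3 days").

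A HAM-D17 is also taken at day -8, before allocation, but {20a} does not use it as the baseline.

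**The concern.** The endpoint compares two clinician ratings. At day 28 the rater knows the arm, by the plan's own statement. At day 0 the score is tied to first intake rather than to randomisation. A physician could therefore learn the allocation, receive the arm A recommendation, score the baseline and then start the drug, all within the rules.

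Response is a yes/no threshold at half the baseline. A slightly higher day-0 score or a slightly lower day-28 score in one arm moves patients across it without any difference in outcome. Time to response, remission and HAM-D17 change ({12}) use the same ratings. No analysis plan can restore a pre-allocation baseline once scores have been collected otherwise, so the order has to be fixed at collection.

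**Working it through.** **1. The plan's own figure.** Inputs from {14}: response 0.5 and 0.7, power 80%, α = 5% (two-sided per {20a}). With pooled variance and no continuity correction, n = [1.960·√(2·0.6·0.4) + 0.8416·√(0.25 + 0.21)]² / 0.2² = (1.358 + 0.571)² / 0.04 ≈ 93 per arm. The stated 95 gives 80.8% power by the same approximation. The sample size is not in dispute and does not change with the fix.

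**2. What the text allows on day 0.**

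| Event | Timing rule in the visible text |
|---|---|
| Decision leading to randomisation | day 0 (±3 days) |
| Arm A recommendation sent | day 0 |
| Baseline HAM-D17 | day 0 (±3 days), before first intake |
| Start of new drug | day 0 |

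The only fixed order for the baseline is score before first intake. Nothing places the score before randomisation or before the recommendation.

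**3. From score shift to response rate.** Assumption, not in the documents: the day-28 score is normal, centred at half the baseline, with SD 6 to 7, so that 50% respond without bias, as in {14}. Raising the recorded baseline by 2 points raises the 50% cut-off by 1 point, so the response rate becomes Φ(1/SD). The baseline mean cancels.
- SD 6: Φ(0.167) = 0.566
- SD 6.5: Φ(0.154) = 0.561
- SD 7: Φ(0.143) = 0.557

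The gain is 5.7 to 6.6 percentage points. A day-28 score 1 point lower has the same effect, so a point of drift at day 28 counts twice as much as a point at baseline.

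**4. From response-rate artefact to false positives.** Exact rejection probability of the two-sided Fisher test at 0.05 with 95 per arm: the sum over all x, y of Bin(x; 95, p_A)·Bin(y; 95, p_B) where the Fisher p ≤ 0.05. With p_B = 0.50 and no true effect:

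| Artefact in arm A | Rejection |
|---|---|
| none | 3.5% |
| 5 points | 8.0% |
| 10 points | 23.3% |
| 15 points | 48.9% |

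**5. Both ends together.** Simulation with whole-number scores. Assumed: baseline mean 23, SD 4; day-28 residual SD 6; unbiased response 51.6%; shifts in arm A only.

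| Baseline higher by | Day 28 lower by | Gap (percentage points) | Rejection |
|---|---|---|---|
| 1 | 0 | 3.3 | 5.4% |
| 2 | 0 | 6.6 | 11.5% |
| 0 | 1 | 6.6 | 11.5% |
| 1 | 1 | 9.7 | 22.2% |

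These tables show sensitivity only. No section supports a particular size or direction of shift.

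**The case against.** **The baseline part argues from silence.** Footnote a sets a latest time; it does not put the score after allocation. There are weak signs the other way. The day-0 HAM-D17 is also taken in the observational arm, so it does not depend on randomisation. Randomisation is a separate electronic step by a clinical pharmacist ({16b}, {16c}), after the physician has decided that a new drug is needed. Fig. 1 is not shown, and the full protocol may give the order. This stands in part. A reader might infer that baselines are scored after allocation; the documents do not say so. They do set an anchor, and first intake is the wrong one for this purpose.

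**Open label is a disclosed choice.** True, and {18a} is candid about the rater. But open-label treatment does not prevent scoring before randomisation. The limitation in the Discussion names physician and patient, not the rater or the order of baseline scoring.

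**Masked raters may not be feasible.** This largely stands. Section {18a} applies its statement on blinding to raters in general and does not say that designated personnel are outside the treating team. No rater staffing is given. Patients know their arm and may reveal it at interview.

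**The magnitude is assumed.** This stands; a one-sided 2-point shift is a chosen scenario.

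**Two tempting extensions fail.** One is that a post-randomisation baseline is an invalid covariate. That does not bear on an unadjusted Fisher test, and {20b} plans no adjusted analyses. The other is to rest the primary result on masked ratings only. That would select patients after randomisation and lose the randomised comparison.

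**Conclusion.** The point holds in a limited form. The unblinded day-28 rating is explicit. For day 0, the visible text permits a baseline scored with the allocation known; it does not show that this happens. Together they leave an avoidable route to bias in the primary endpoint.

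With an assumed SD of 6 to 7, a 2-point baseline inflation confined to arm A adds about 6 percentage points to its response rate. A 5- or 10-point artefact takes the false-positive rate from 3.5% to 8.0% or 23.3%. The real bias could be nil or run either way, so the figures do not support a reading that the trial's result will be biased in favour of the PGx arm. The change should be made because fixing the baseline order costs little; the trial remains interpretable without it.

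**What to change.** 1. Reword footnote a so that the day-0 HAM-D17 is scored and recorded, with date and time, before randomisation. Have the clinical pharmacist confirm in secuTrial that it has been recorded before randomising. A confirmation is enough: scores are first recorded on paper or in the medical record and transferred later ({18a}, {19}), so requiring the score itself in the database would demand real-time entry.
2. Where designated personnel not involved in the patient's treatment are already available, prefer them for the day-28 rating and do not tell them the arm.
3. For every rating, record who rated and whether the arm was known. Report this descriptively by arm, and keep all randomised patients in the primary comparison whatever the rater knew.
4. Reword {17a} so that it does not suggest that blinding of the outcome rater is unnecessary.

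**Cost.** Items 1 and 4 need wording and one confirmation step; items 2 and 3 need some rota planning and an extra field on the form. Masking will be partial. Recruitment began in September 2020 (Trial status), so the changes reach only later patients, should start in both arms at the same time, and may need ethics approval as a substantial change ({25}). The sample size stays at 95 per arm.

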##### Observational arm

If after the run-in phase, at day 0 (±3 days), the adjustment to a new antidepressant pharmacotherapy is evaluated by the treating investigator as not necessary, the patient will be followed up in the observational arm, and the following scores will be assessed on days 0, 14, and 28 ±3 days: (1) HAM-D17, (2) FIBSER, and (3) BDI-II. Additionally, also blood samples will be collected on days 14 and 28 (±3 days) for further genotyping and retrospective assessment of serum drug concentrations (see Fig. 1). After day 28 of the study, the already collected genotyping data will be interpreted by a clinical pharmacist and made accessible to the treating physician.

##### Randomization and procedures for arms A and B

If after the run-in phase, at day 0 (±3 days), the treating physician assesses the adjustment to a new antidepressant pharmacotherapy as necessary, and the patient is randomized to either arm A (intervention group) or arm B (control group) (see Fig. 1).

In arm B, the treating physician alone, according to the current standard of care considering clinical factors only, will determine the selection and dosing of the new antidepressant pharmacotherapy. The treating physician and patient will be blinded to the results of the previously conducted pharmacogenotyping for patients randomized to arm B until day 28. For patients in arm B, results from prior pharmacogenetic testing will be interpreted by a clinical pharmacist and made accessible to the treating physician after day 28.

In arm A, a clinical pharmacist will process and evaluate the results from PGx testing (Stratipharm®) in context of the individual patient history as well as current co-medication and forward an individualized recommendation for antidepressant selection and dosing to the treating physician at day 0.

In both arms, the newly prescribed antidepressant pharmacotherapy intake is continuously documented and therapy response observed over a period of 28 days with weekly assessments of adverse events related to the antidepressant medication (using CTCAE version 5.0) and scorings of HAM-D17 (days 0, 7, 14, 21, and 28; ±3 days) as well as patient self-assessments of FIBSER score (days 0, 7, 14, 21, and 28; ±3 days) and BDI-II score (days 0, 14, and 28; ±3 days) (see Table 1).

If patients in either study group remain in the clinic after day 28 (±3 days), a weekly follow-up of HAM-D17, FIBSER, and two-weekly BDI-II are continued until discharge (see Table 1).

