#### Provisions for post-trial care {30}

After the intervention phase of the study, patients in the control and observation groups as well as their treating physicians will gain access to the PGx data collected.

Study participants do not receive any compensation. However, there are no additional costs for the study participants or the respective health insurance company due to study participation.

In the event of study-related damage or injuries, the liability of the respective institution, Psychiatric Services Solothurn or Private Clinic Wyss, provides compensation, except for claims that arise from misconduct or gross negligence.

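### Control-arm genotype results may be released once day 28 has passed, but the primary HAM-D17 rating may be made up to day 31

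*Protocol article*

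**What the plan says.** **Release of the genotype result.** Under Randomization and procedures for arms A and B: "The treating physician and patient will be blinded to the results of the previously conducted pharmacogenotyping for patients randomized to arm B until day 28". The next sentence states that "results from prior pharmacogenetic testing will be interpreted by a clinical pharmacist and made accessible to the treating physician after day 28". Section {17a} extends release to patients and to the observational arm: the data "will only be shared with the treating physician and patients allocated to the control or observational group after day 28 of the treatment phase". The section on the observational arm uses the same bare day 28. Section {30} names a phase and no day: "After the intervention phase of the study, patients in the control and observation groups as well as their treating physicians will gain access".

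**Timing of the final rating.** Arms A and B have "scorings of HAM-D17 (days 0, 7, 14, 21, and 28; ±3 days"; FIBSER and BDI-II carry the same tolerance at day 28. Section {20a} fixes the endpoint: "The primary outcome of this study is the response rate at day 28 in study arms A and B".

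**Who rates.** Section {18a}: "The HAM-D17 score is assessed by a trained rater (e.g., treating physician or specifically designated personnel". The same section says that this rater knows the allocation and that patients complete FIBSER and BDI-II themselves.

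**The concern.** Release is governed by a calendar day and the rating by a window around that day. The two rules overlap, and nothing sets their order.

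This matters because withholding the genotype is the only masking left after allocation. Section {16b} treats it as worth protecting: access to the genetic data is restricted by password to the appointed pharmacists. The people who receive the result can also be the people who score. A physician or patient told that the current drug fits the genotype poorly may rate the outcome worse, and one told that it fits well may rate it better. The timing is one-sided. Arm A's physician has the recommendation from day 0, so in the randomized comparison only arm B can have new genotype information arrive between day 28 and the final rating. Response is a cut-off (a HAM-D17 fall of half or more), so a small shift near the threshold can change a patient's classification.

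**Working it through.** The check is mainly a comparison of dates.

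1. **Rating window** (Randomization and procedures for arms A and B): 28 − 3 = day 25 to 28 + 3 = day 31, which is 7 permitted days.
2. **Release point** (same section and {17a}): after day 28, so day 29 at the earliest.
3. **Overlap:** days 29, 30 and 31, which is 3 of 7 permitted days.
4. **Is release tied to the rating anywhere?** The four places that mention release are {30}, the observational arm section, the section on arms A and B, and {17a}. None makes it depend on a completed assessment.
5. **Could day 28 mean the whole window?** The section on arms A and B adds the three-day tolerance to day 28 when it describes the ratings and the start of weekly follow-up, but not in the release rule. The observational arm section does the same: tolerance for scores and blood samples, none for release. The wording favours the literal reading without settling it.

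**The plan's sample size, for scale.** Section {14} gives 95 per arm from response rates of 0.5 and 0.7, two-sided α = 0.05 and 80% power. With the usual two-proportion formula and pooled variance under the null:

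n = [1.960 × √(2 × 0.6 × 0.4) + 0.842 × √(0.25 + 0.21)]² / 0.2² = (1.358 + 0.571)² / 0.04 ≈ 93 per arm.

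This is within two patients of 95, and the point does not affect it.

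**What one changed classification does.** One arm B patient scored as a non-responder instead of a responder moves the difference by 1/95 = 1.05 percentage points. From the planned 20.0 points, one such patient gives 21.1 and five give 20.0 + 5 × 1.05 = 25.3. A change the other way narrows the difference by the same amount. The counts of one and five are assumptions to show scale. The documents give neither the spread of actual rating days, nor the delay before release, nor the size of any shift in scoring.

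**The case against.** **Day 28 may be a visit label.** Table 1 makes day 28 the last column of the treatment phase, {17a} refers to day 28 of that phase, and {30} speaks of the end of the intervention phase. If release was meant to follow the day-28 visit, the gap closes. This reading is possible, but the contrast in step 5 of the working tells against it, and a site may fairly follow the literal text.

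**Release is not automatic on day 29.** A pharmacist must first interpret the result. This stands as a practical brake, but no minimum delay is stated.

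**The trial is open-label.** Physician and patient know the arm, and the rater is not masked. This stands, and it limits the added exposure to the genotype result itself, over at most three days. Knowing the arm is still different from knowing how well this patient's drug fits.

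**The article condenses a longer protocol.** The full document may contain a release trigger. The concern here, however, is a stated rule that permits the wrong order, not an omitted detail.

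Three stronger inferences are tempting and are not supported:

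- A reader might infer that 3/7, or about 43%, of arm B ratings (3/7 × 95 ≈ 41 patients) would follow disclosure. That needs ratings spread evenly over the window and release before each late rating. The documents support neither.
- A reader might extend the point to adverse event grading. The protocol calls that assessment weekly and does not clearly attach the three-day window to it.
- A reader might infer that treatment changes made on the disclosed result would contaminate the control arm. The background section says that at least four weeks of drug exposure are needed to judge response, so a change one to three days before rating could hardly move the endpoint.

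**Conclusion.** The point holds as a defect in a stated rule. Taken literally, the protocol allows the interpreted genotype result to reach the physician and patient in arm B before the final HAM-D17, BDI-II and FIBSER ratings, on three of the seven permitted rating days. The HAM-D17 rating is the primary endpoint, so the order should be fixed.

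The conclusion assumes that day 28 in the release rule means the calendar day. The number of affected patients, the direction of the net bias and its size cannot be derived from the documents. The effect is probably modest next to the open-label rating that the protocol already discloses. The observational arm has the same gap, but it does not contribute to the primary endpoint. The sample size does not need to change.

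**What to change.** In section {30}, the observational arm section, the section on arms A and B, and {17a}, replace the bare day 28 (or the bare phase) with one rule. Genotype results for arm B and the observational arm are released only after the day-28 HAM-D17, BDI-II and FIBSER are completed and recorded. If that visit is missed, they are released after the window closes on day 31. Log the release date for each patient so that the order can be checked.

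For patients already past day 28, report how many arm B ratings were made after release. If there are any, a sensitivity analysis should keep every randomized patient, for example by using the last HAM-D17 before release. That matches the last-observed-value rule in {20c}. It takes an earlier rating for the affected arm B patients, which may understate their response if they were still improving, and this should be stated. Do not drop those patients: removing people from one arm because of an event after randomization breaks the randomized comparison.

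The cost is one sentence repeated in four places and one date field. Control and observational patients may get their results up to about three days later.

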### Objectives {7}

We hypothesize that it is beneficial to incorporate PGx information to guide drug selection and dosing in the treatment of depression, involving clinical pharmacists in processing and evaluating the PGx test results in the context of the individual patient history and current co-medication.

The primary objective of this clinical study is to compare the service of pharmacist-guided PGx testing with the current standard of care for antidepressant selection and dosing with regard to treatment outcome. Accordingly, the following null hypothesis results for the primary endpoint: Therapy response rates after antidepressant treatment for 4 weeks do not differ whether the service of pharmacist-guided pre-emptive pharmacogenetic testing was applied or not.

The secondary objectives are to compare tolerability of the antidepressant pharmacotherapy and overall duration of hospitalization between the intervention and standard care study arms.

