### Interventions

#### Explanation for the choice of comparators {6b}

The intervention described in the following section {11a} is compared with the current standard of care, where the treating investigator alone selects and doses the antidepressant pharmacotherapy, considering clinical factors only, without taking genetics into account.

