#### Relevant concomitant care permitted or prohibited during the trial {11d}

The introduction of a new antidepressant pharmacotherapy or augmentation strategy (e.g., lithium and the like) are not possible until after randomization when genotyping results are available (7±2 days after inclusion). However, the following measures can be taken in the interim: (1) if an antidepressant therapy has already been taken before entering the clinic, it can be continued during this period, and (2) additional supportive measures are possible, including sleep-promoting pharmacotherapy (e.g., benzodiazepines or low-dose trazodone, mirtazapine, trimipramine).

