#### Outcomes {12}

The primary endpoint is defined as the rate of response to the antidepressant therapy at the end of week 4 of the treatment phase. This time point was chosen based on the recommendations of the SGAD, which advise to assess clinical effectiveness after four weeks of antidepressant pharmacotherapy [3]. Moreover, the response is determined as a reduction in the Hamilton Depression (HAM-D) Scale score of at least 50% from the baseline score [18]. In this study, the 17-item HAM-D questionnaire (HAM-D17) is used.

Secondary endpoints will be assessed to further evaluate the clinical effectiveness of pharmacist-guided PGx testing as an intervention in antidepressant pharmacotherapy. Included are the following endpoints: (1) time to response—time span from the start of antidepressant pharmacotherapy until first assessed response (= HAM-D17 reduction of at least 50% compared to baseline), until end of week 4; (2) remission rate—HAM-D17 score ≤ 8, at week 4; (3) overall change in HAM-D17 score from baseline to end of week 4; (4) time till discharge—time span from admission to discharge from inpatient treatment, assessed up to 3 months; (5) patient depression self-rating—two weekly assessment with Beck-Depression-Inventory (BDI-II) questionnaire [19], until end of week 4; (6) side effect measure—weekly assessment of self-rated frequency, intensity, and burden of side effects (FIBSER score) [20], until end of week 4; and (7) Number of AEs related to antidepressant pharmacotherapy—severity grading ≥ 2 (using CTCAE version 5.0) [21] and causality to antidepressant pharmacotherapy assessed as possible, probable, or definite, until end of week 4.

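### Time till discharge runs to 3 months under the label intervention versus standard care, but arm B gains PGx access after day 28, so for longer stays the contrast is immediate versus delayed access

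*Protocol article*

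**What the plan says.** Objectives {7} names two secondary objectives, tolerability and a comparison of "overall duration of hospitalization between the intervention and standard care study arms". Outcomes {12} defines the matching endpoint as "time till discharge—time span from admission to discharge from inpatient treatment, assessed up to 3 months". The comparator section {6b} describes standard care as the investigator choosing alone, "considering clinical factors only, without taking genetics into account".

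Three places set the release of genotype information to controls. Under the procedures for arms A and B, arm B's "results from prior pharmacogenetic testing will be interpreted by a clinical pharmacist and made accessible to the treating physician after day 28". Section {30} says that "patients in the control and observation groups as well as their treating physicians will gain access to the PGx data collected" once the intervention phase is over. Section {17a} states that genetic data are shared with physicians and patients "allocated to the control or observational group after day 28 of the treatment phase".

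Stays beyond day 28 are foreseen: the procedures section and Table 1 continue assessments at days 35, 42 and onward until discharge. The primary endpoint and the other six secondary endpoints stop at week 4. Only time till discharge runs past the release.

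**The concern.** From the release on, an arm B inpatient no longer meets the article's own definition of standard care, yet the endpoint keeps that label to 3 months. If PGx guidance shortens stay and some arm B physicians act on the late result, the observed difference shrinks. A null finding could then mean that PGx guidance does not shorten stay, or that late arm B stays were themselves informed by PGx, and the analysis as described could not separate the two. Nothing in the article limits the endpoint to day 28 or describes it as early against delayed access.

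A smaller matter is the time origin. The clock starts at admission, but allocation happens at day 0, after the genotyping run-in. That first stretch cannot be affected by allocation and adds only noise.

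**Working it through.** **The plan's own figure.** None is given for time till discharge. The 95 per arm in {14} concerns day-28 response, 0.5 versus 0.7, two-sided 5%, 80% power. With a pooled rate of 0.6: n = [1.96·√(2·0.6·0.4) + 0.8416·√(0.25 + 0.21)]² / 0.2² = (1.3579 + 0.5708)² / 0.04 = 93. The stated 95 is therefore reproduced within 2 patients and is not touched by this point.

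**How much of the window lies after release.** Section {11d} puts genotyping results 7±2 days after inclusion, and day 0 has a ±3-day window. Assuming inclusion close to admission, day 0 falls about 5-12 days into the stay and day 28 falls at day 33-40. Of about 91 days, 91 − 40 = 51 to 91 − 33 = 58 lie after release, or 56-64%.

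**Size of dilution (illustration; every input is assumed).** Exponential discharge after randomisation, with control median m = 28, 35 or 42 days and λ = ln 2 / m. Arm A's discharge hazard is hλ, with h = 1.3 or 1.5. Follow-up is T = 82 days (91 less about 9 days before randomisation). Mean inpatient days up to T:

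- Arm A: (1 − e^(−hλT)) / (hλ)
- Arm B, no uptake: (1 − e^(−λT)) / λ
- Arm B, full uptake acting from day c: (1 − e^(−λc)) / λ + e^(−λc)·(1 − e^(−hλ(T−c))) / (hλ)

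Example, m = 28 and h = 1.5: arm A 25.65 days; arm B 35.09 with no uptake, 34.47 with c = 56, 31.85 with c = 28. The differences are 9.44, 8.82 and 6.20 days, so dilution is 0, 6.6% and 34.3%. The case c = 56 reflects the Background {6a} statement that at least 4 weeks of drug exposure are needed to assess response.

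| m | h | Arm B inpatient at day 28 | Difference, no uptake | c = 56 (dilution) | c = 28 (dilution) | Difference up to day 28 only |
|---|---|---|---|---|---|---|
| 28 | 1.3 | 50% | 6.24 | 5.85 (6.2%) | 4.15 (33.5%) | 1.74 |
| 28 | 1.5 | 50% | 9.44 | 8.82 (6.6%) | 6.20 (34.3%) | 2.79 |
| 35 | 1.3 | 57% | 6.40 | 5.95 (7.0%) | 4.11 (35.8%) | 1.54 |
| 35 | 1.5 | 57% | 9.82 | 9.10 (7.4%) | 6.22 (36.7%) | 2.48 |
| 42 | 1.3 | 63% | 6.35 | 5.87 (7.6%) | 3.98 (37.3%) | 1.37 |
| 42 | 1.5 | 63% | 9.85 | 9.07 (7.9%) | 6.09 (38.1%) | 2.22 |

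**Power of the alternatives.** Log-rank, 95 per arm, power ≈ Φ(ln HR·√d / 2 − 1.96) with d discharges. Under full uptake at day 28, ln HR is multiplied by the share of discharges occurring by day 28.

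| h | 3 months, no uptake | 3 months, full uptake at day 28 | Censored at day 28 |
|---|---|---|---|
| 1.3 | 36-40% | 13-18% | 21-27% |
| 1.5 | 71-76% | 26-38% | 45-56% |

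Which analysis is stronger thus depends on an uptake that nobody knows in advance.

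**The case against.** A reader might infer that the later part of the endpoint compares treated with treated patients. The documents do not support that. Section {11a} defines the intervention as pre-emptive, applied before the new antidepressant is started. Arm B's drug was chosen at day 0 without PGx, and later its results are only made accessible; no change of therapy is stated. The randomised comparison of a pre-emptive service with none at drug selection remains valid to discharge. This part of the objection stands, and immediate versus delayed access is the accurate description.

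A reader might also take the dilution to be about a third. That needs every arm B inpatient to gain the full effect on day 28, which sits badly with the 4-week exposure in the Background. With an effect only from day 56 the loss is 6-8%, and without uptake it is nil.

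Nor should a day-28 analysis replace the 3-month one. In the model, 50-63% of arm B are still inpatients at day 28 and the difference up to then is only 1.4-2.8 days, so it would no longer measure overall duration of hospitalisation. If arm A's benefit also takes 4 weeks, it might show nothing.

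Finally, counting from admission does not bias the difference in mean stay, since time before randomisation is balanced in expectation, and total stay is a natural measure of resource use. It only adds variance.

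None of this removes the mismatch between the label and the comparison. Objective, window and release rule are all stated in the article, so the mismatch is not a detail left to a fuller plan.

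**Conclusion.** The point holds in limited form. Time till discharge is labelled intervention versus standard care, but for patients in hospital beyond day 28 it compares immediate pre-emptive with 28-day-delayed PGx access. If PGx guidance helps, the difference may be diluted, by anything from nothing to about 33-38% under the assumed stay distribution and hazard ratios. The article gives neither length of stay nor uptake, so the size cannot be narrowed. Dilution of a benefit works toward no difference; the risk is a misread null result, not a spurious benefit. It concerns one secondary endpoint, though one that carries a named secondary objective. The correction changes what that endpoint can conclude at almost no cost, so it should be made.

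**What to change.** In {12} and {20a}:

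1. Keep the 3-month comparison, but define and interpret it as immediate versus 28-day-delayed PGx access. State that a null result does not show that PGx guidance fails to shorten stay compared with standard care.
2. Start the clock at randomisation, and report stay from admission descriptively.
3. Add a supportive comparison censored at day 28 (log-rank or restricted mean inpatient days), the only part free of the release.
4. Report arm B antidepressant changes after release, from the medication records that Table 1 already keeps to discharge. This shows where between no uptake and full uptake the trial lies.

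The cost is wording and a little extra analysis, and the day-28 comparison will have low power. No new data are needed, the sample size stays at 95 per arm, and the release of results to arm B stays as planned.
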